# The PAPHIO study protocol: a randomised controlled trial with a 2 x 2 crossover design of physical activity adherence, psychological health and immunological outcomes in breast cancer survivors

**DOI:** 10.1186/s12889-020-08827-x

**Published:** 2020-05-15

**Keywords:** Breast cancer survivor, Self-directed physical activity, Physical activity adherence, Motivational interviewing, Pedometer, Quality of life, Psychological health, And immunological biomarker

## Abstract

**Background:**

The PAPHIO study; a randomized controlled trial with 2X2 crossover design will implement a self-directed physical activity program in which participants will engage in self-monitoring and receive motivational interviewing to enhance physical activity adherence. The study aims to determine the effects of 24 weeks self-directed activity combined with motivational interviewing (MI) on (i) psychological health, (ii) quality of life (QoL) and (iii) immune function in female breast cancer survivors.

**Methods:**

The study will recruit 64 female breast cancer survivors within 3 years of diagnosis and at least 6 months post primary treatments at Western Health Sunshine Hospital, Melbourne, Australia. They will be randomly allocated to immediate intervention (IIG group) or delayed intervention groups (DIG group) in a 1:1 ratio. All participants will be given a wearable device (Fitbit Alta HR) and undertake self-directed physical activity for 24 weeks and will receive MI for 12 weeks (IIG; during week 0 to week 12 and DIG; during week 13 to week 24). Participants’ daily step count and the changes of immune cell functionality will be assessed at the beginning (week 1: T1), week 12 (T2) and week 24 (T3) of the program. Physical activity adherence will be assessed at T2 and T3. Participants will also complete four questionnaires assessing exercise self-regulation (BREQ2), exercise barrier and task self-efficacy, mental health (DASS-21) and QoL (FACT-B) at three time points (T1 to T3). Linear-mixed models will be used to assess the relationship between physical activity volume by step counting and mental health (DASS-21), QoL (FACT-B), immune biomarkers, self-regulation (BREQ2) and self-efficacy at T1, T2 and T3;between 2 groups.

**Discussion:**

We expect this physical activity intervention to be acceptable and beneficial to the participants in terms of psychological and immunological well-being with the potential outcomes to be implemented more widely at relatively low cost to these or other patient populations.

**Trial registration:**

Australian New Zealand Clinical trials Registry- ACTRN12619001271190. Prospectively registered on 13 September 2019.

## Background

Breast cancer is a common malignant disease leading to physical and psychological distress in females worldwide [1, 2]. Approximately 2.1 million women suffered from this disease and 626,000 deceased across the world in 2018 [3]. . The occurrence rate of breast cancer has dramatically increased in 22 out of 39 countries from 2008 to 2012, whereas the global death rate has gradually dropped [4]. The global trend of breast cancer increases awareness in the availability of breast cancer care program [4].

Breast cancer survivors may have mental distress mainly due to long-term treatments [5].Currently, survivorship programs, especially physical activity programs have emphasised strategies to enhance psychosocial well-being [6, 7]. Psychological interventions including emotional ventilation, adjustment skill training and self-efficacy promotion techniques have been applied in improving their mental wellness over the decades [6, 8].

Physical activity, especially moderate intensity aerobic exercise for female breast cancer survivors, have been noted in a number of studies to be beneficial to breast cancer outcomes, decreasing the mortality rate by > 30% and reducing the recurrence rate [9]. As a result of physical activity, there is a reduction in the total body fat as well as a number of inflammatory and immunological biomarkers which could contribute to better outcomes in breast cancer survivors [10, 11]. Moderate aerobic exercise and combination of aerobic and resistant training in breast cancer women ranging between 15 and 24 weeks could possibly activate immune cells such as NK cell cytotoxic activity and lymphocytes [12, 13]. Furthermore, a 12-weeks aerobic exercise training at home in breast cancer survivors reduces the level of epithelial neutrophil activating protein and pro-inflammatory cytokines [14].

Approximately one third of patients with cancer reduce their physical activity after diagnosis and almost 70% of them will not reach the exercise recommendation for cancer patients [15].. 30% Of breast cancer survivors with early phase (stage 0 to 3) breast cancer have reported physical activity cessation during 12 months follow-up after participation in a 6 months RCT [16]. The cessation may be associated with the resumption of their previous domestic tasks and work [16]. Physical activity barriers in older breast cancer survivors are related to physical tiredness and lack of time management skills [17]. In addition, some breast cancer survivors have low confidence in the benefits of physical activity in minimizing adverse effects of breast cancer and treatment [18]. The challenge of recruiting patients with advanced stage of cancer is to deal with their cancer-related fatigue in particular the side effect of treatments [15].

### Physical activity and motivation for activity adherence in breast cancer survivors

Adoption and adherence to physical activity programs amongst cancer survivors are challenging due to their physical and mental vulnerability [19]. As such, in this study we developed an intervention which maximizes feasibility, sustainability and generalisability. This study will prescribe self-directed physical activity to breast cancer survivors. Many of self-directed techniques for physical activity adherence in participants with advanced stage of heterogeneous cancers have been used in research studies, such as partially advised and home-based program, exercise class teaching and peer support walking group programs [20]. Many of the programs have achieved high percentages of exercise adherence, reducing fatigue and improving QoL [20].

An important factor to adopt and adhere to a physical activity program is an individual’s motivation. To this end, a number of behavioural change strategies have been reported which enhance motivation and adherence [21]. Two of these strategies are Motivational Interviewing (MI) and self-monitoring. MI is a conversation technique used by a professional during consultation when making health behaviour changes [22], and has been effectively used to bring about behavioural change in health promotion programs for the general population. This includes changes in eating behaviour, alcohol cessation and adoption of an active life style [23]. More specifically, face-to-face and phone based MI has been implemented successfully to enhance self-efficacy and reduce resistance against physical activity in breast cancer survivors [24, 25].. On the other hand, self-monitoring,one of the important concepts in self-regulation theory, is an auditing mechanism of individual performance in relation to an individual’s cognitions, beliefs and emotions [26]. Some digital devices have the ability to promote physical activity through self-monitoring concept [27]. For example, step counting gadgets including pedometers, can effectively monitor physical activity in terms of daily steps. Such devices have been utilised for promotion of physical activity in clinical trials [28] especially in breast cancer patients and survivors [29, 30]. Step counters help in monitoring individual’s physical activity behaviour and can result in increased motivation and ultimately adherence to long-term physical activity behaviour [31].

To understand participants’ motivation to self-directed physical activity, self-determination theory (SDT) has been effectively used to enhance insight in physical activity behaviour and motivation in breast cancer survivors [32]. According to SDT motivation to engage in behaviour lies on a continuum ranging from extrinsic (controlled by external factors) to intrinsic (individual interest and preference). The theory predicts that intrinsic-motivation might enhance confidence in task accomplishment (competence), independent action (autonomy) and the feeling of connection to others (relatedness) [32]. Our study will assess how self-regulation and motivational interviewing might change participants motivational orientation over the intervention period using the behavioural regulations in exercise questionnaire (BREQ2 [33];).

Self-efficacy, an important concept in social cognitive theory, has been shown to be a predictor for physical activity behaviour and adherence in breast cancer patient [34]. In this project two types of efficacy beliefs will be examined. First, we will explore exercise barriers self-efficacy, which will examine the participants’ confidence to overcome or deal with barriers to their exercise participation. Secondly, this project will examine task self-efficacy beliefs In particular, it will examine the self-efficacy beliefs of the participants to engage in exercise behavior [34]. To measure this, the project will use the nine-item barriers self-efficacy [34] and four-item task self-efficacy questionnaire [34].

### Study goals and objectives

The study has an overall aim to determine the effects of 24 weeks self-directed activity combined with motivational interviewing on (i) psychological health (depression, anxiety, stress), (ii) quality of life (QoL; physical, social/family, emotional and functional) and (iii) immune function in female breast cancer survivors. In addition, we will explore the dose-response relationship between exercise volume (step count) and the outcome measures.

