### Randomisation

The study design is a two-armed RCT with a crossover design. Sequence generation will be conducted by simple randomisation following patient informed consent. The participants will be randomly allocated to either IIG or DIG in 1:1 ratio by computerised number generator. Allocation concealment by enclosing the allocation in sealed envelopes will be used to prevent selection bias [37]. The allocation concealment will be conducted by a third party to prevent researchers from affecting group assignment. The participants in both groups will be prescribed a self-directed physical activity for 24 weeks. The IIG will receive MI from week 1 to week 12, whereas DIG will receive the same MI intervention from weeks 13 to 24.Allocation concealment technique will be applied in process of randomisation. During weeks 1 to week 12, theIIG will perform self-directed physical activity and receive MI. On the other hand, the DIG will perform self-directed physical activity without MI. During week 13 to week 24, DIG will continue self-directed physical activity with MI. Whereas IIG will perform physical activity but will no longer be given MI.

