#### Analysis of data

Baseline descriptive statistics (mean, standard deviation for continuous data and percentage for categorical data) will be used to describe the distribution of personal data and variables between two groups of participant (e.g., age, breast cancer health history, body compositions, and blood pressure). Independent T-test will be used to compare means for continuous data and the Pearson Chi square will be used for testing the difference in distribution of a categorical variable at baseline [49].

Linear-mixed models will be used to identify the relationship between physical activity volume by step counting and mental health (DASS-21), QoL (FACT-B), self-regulation (BREQ2) and self-efficacy at T1, T2 and T3; the relationship between activity volume by step counting and immune biomarker changes at T1,T2, and T3. The models will also be used to control for the effect of covariates or confounding factors and to manage for missing data.

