## Discussion

Self-directed physical activity in this clinical trial is considered a feasible practice in breast cancer survivors. More specifically, the combination of self-monitoring (step count) and MI have been shown to be important strategies for long-term adherence to physical activity behaviour in people living with cancer. This trial, will examine the efficacy of these health behaviour change techniques in self-directed physical activity. This is an important issue because this is a potentially low cost intervention which could be applied and implemented widely if successful. This study is guided by the Self-Determination Theory [32] and Social Cognitive Theory [26]. We anticipate that those who adhere to the program will be more intrinsically motivated at the end of the trial in comparison to those who do not. We will also explore whether the initial motivational orientation predicts adherence to the physical activity program. In addition, we would anticipate that successful adherence to the physical activity program will be associated with higher levels self-efficacy believes and reduced number of barriers to be physically active.

The primary outcomes of this study focuses on both psychological and physiological changes which can translate positively for their breast cancer clinical outcomes. The study expects the enhancement of their QoL, psychological health and immune biomarkers in 12 to 24 weeks self-directed physical activity by pedometor application combining 12 weeks motivational interviewing.

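### The stated aim is the effect of 24 weeks of activity plus MI, but both arms do the activity throughout, so randomisation supports only the effect of adding MI

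*Protocol article*

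**What the plan says.** Under Study goals and objectives the protocol article states: "The study has an overall aim to determine the effects of 24 weeks self-directed activity combined with motivational interviewing". The outcomes named are psychological health, QoL and immune function. The Background part of the Abstract gives the same aim.

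The Randomisation section describes the arms. The design is given as follows: "The study design is a two-armed RCT with a crossover design". On activity: "The participants in both groups will be prescribed a self-directed physical activity for 24 weeks". On MI: "The IIG will receive MI from week 1 to week 12, whereas DIG will receive the same MI intervention from weeks 13 to 24". In the first 12 weeks "the DIG will perform self-directed physical activity without MI". For the second 12 weeks the section says: "Whereas IIG will perform physical activity but will no longer be given MI". The Abstract and the Study design section describe the same arrangement.

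The Discussion sets out the anticipated result: "The study expects the enhancement of their QoL, psychological health and immune biomarkers in 12 to 24 weeks self-directed physical activity", in combination with 12 weeks of MI.

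The Analysis of data section says: "Linear-mixed models will be used to identify the relationship between physical activity volume by step counting and mental health (DASS-21), QoL (FACT-B" and the remaining outcomes. The Abstract adds that this is to be done between the two groups.

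**The concern.** The aim and the Discussion's expectation are about a package, activity plus MI over 24 weeks. To estimate the effect of a package by randomisation, some participants must be without it for some period. Here nobody is ever without the activity, and by week 24 everyone has had both parts.

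What is at stake is the conclusion the trial may draw. A statement that the programme improves QoL, mood or immune markers would have to rest on change from T1 to T3 in women who all received it. Women may enter from 6 months after active treatment, so some change could occur without any programme. The question that randomisation can answer, whether MI adds anything to Fitbit-supported activity, is not how the aim for the primary outcomes is worded.

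**Working it through.** The plan gives no figure that settles this point, so the check compares exposure by arm and then asks what each contrast identifies.

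**Step 1. Exposure by arm** (Randomisation section; cumulative weeks)

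| Time | Component | IIG | DIG | Difference |
|---|---|---|---|---|
| T2 (week 12) | activity | 12 | 12 | 0 |
| T2 (week 12) | MI | 12 | 0 | 12 |
| T3 (week 24) | activity | 24 | 24 | 0 |
| T3 (week 24) | MI | 12 | 12 | 0 (order only) |

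The activity difference is zero at both times. MI lasts 12 weeks in each arm, so nobody has 24 weeks of both together.

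**Step 2. What each comparison identifies.** Let b be the baseline mean, α₁ and α₂ the effect of activity by T2 and T3, s₁ and s₂ the background change that would occur anyway, τ the effect of MI while it is given (taken as equal in both periods), and λ the part of the MI effect that remains in IIG at T3.

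- T2, IIG: b + α₁ + s₁ + τ
- T2, DIG: b + α₁ + s₁
- T3, IIG: b + α₂ + s₂ + λ
- T3, DIG: b + α₂ + s₂ + τ

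The comparisons are then:

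- T2, IIG minus DIG = τ. Activity and background change cancel.
- T3, DIG minus IIG = τ − λ. This is also a randomised comparison, but it is reduced by carry-over.
- Average of the two = [τ + (τ − λ)] / 2 = τ − λ/2. With no carry-over (λ = 0) this is τ. If the MI effect persists in full (λ = τ), the T3 contrast is 0 and the average is τ/2.
- Change from T1 to T3, averaged over the arms = α₂ + s₂ + (τ + λ)/2. The activity effect α₂ appears only in the sum α₂ + s₂, and nothing in the design separates the two.

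No combination of the randomised contrasts contains α₁ or α₂. The package effect is therefore not identified by randomisation, whatever model is fitted.

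**Step 3. Carry-over.** IIG goes directly from MI to no MI, with no washout described, and MI is intended to change behaviour. A value of λ above 0 is plausible, which is why T2 is the cleaner contrast. One condition applies. The Motivational interviewing section lists a DIG session at week 12, while the Randomisation section starts MI for DIG at week 13. T2 is also at week 12, so the two sections need to be reconciled for the T2 contrast to be exactly 12 weeks of MI against none.

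**Step 4. Step-count models.** Step count is measured after randomisation and is not itself allocated. Its association with the outcomes is observational and does not supply the missing activity contrast.

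**The case against.** **The crossover uses both periods.** This stands. Sequence is randomised, so period 2 also carries randomised information on MI. A reader might infer that the only randomised quantity ends at T2; that is too strict. But the extra information is still about MI only, and carry-over weakens it.

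**The article does raise the MI question.** This stands in part. The Discussion says the trial will examine the efficacy of self-monitoring and MI, the Background mentions MI and motivational orientation, and the Abstract refers to a comparison between groups. So the answerable question is not absent from the article. It is absent from the aim as stated for the primary outcomes.

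**No before-after test is planned.** This stands. A reader might infer that the trial will report T1 to T3 improvement as a causal effect. The documents do not say so: the Discussion sentence is an expectation, and the planned models concern step count.

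**Size of possible harm.** It is tempting to note that, with 53 women, a paired test has 80% power for a change of about 0.39 SD, while a two-arm comparison needs about 0.78 SD. That shows nothing about this trial. For any total N the normal-approximation detectable differences are k/√N and 2k/√N, with k = 1.96 + 0.84 = 2.80, so the ratio is always about one half. The documents give no figure for drift. Nor do the eligibility criteria select on extreme FACT-B, DASS-21 or immune values, so the usual reason to expect regression to the mean is absent.

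**A condensed article leaves detail to the full protocol or analysis plan.** This does not answer the point. A fuller plan can choose among the contrasts above, but it cannot create a comparator without activity.

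**Conclusion.** The point holds as a mismatch between the aim and the design. The randomised difference in activity is 0 weeks at both follow-up times, so randomisation can support only the effect of adding MI to Fitbit-supported activity. That effect is cleanest at T2, where MI exposure is 12 weeks against none; a two-period estimate is attenuated by half of any carry-over. T1 to T3 change can be described but is uncontrolled.

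This rests on the exposure pattern in the Randomisation section and, for the carry-over algebra, on an MI effect that is equal in both periods. It does not depend on any assumed drift, and the documents do not show that drift occurs or how large it would be. A reader might also infer that the primary outcome must shrink to FACT-B at week 12. The defect does not require that: all three primary domains can stay. The aim should be corrected because it determines what the trial may conclude; the design itself remains usable for the MI question.

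**What to change.** Restate the primary aim along these lines: to determine the effect of adding 12 weeks of MI to Fitbit-supported self-directed activity on psychological health, QoL and immune function, with IIG versus DIG at T2 as the key comparison. Say that period 2 contributes further randomised information on MI, subject to carry-over. Label T1 to T3 change as uncontrolled and descriptive, and the step-count associations as observational. Bring the Abstract, the Study goals section and the expectation in the Discussion into line.

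The cost is wording: no new arm, visit, participant or outcome. The downside is a narrower headline claim. The sample-size paragraph does not say whether its effect size (d = 2.23 in FACT-B change) refers to the added effect of MI, so that link should be stated when the aim is changed. As an illustration with assumed effects, a simple two-arm comparison with 32 per arm (two-sided 0.05) has power Φ(d√(32/2) − 1.96) = Φ(4d − 1.96): about 0.22 at d = 0.3, 0.52 at d = 0.5 and 0.89 at d = 0.8.

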### Study design

This study is a randomised crossover trial; a single site research project conducted at Brest Cancer Service Clinic, Western Health (Sunshine Hospital) Australia. Potential participants will be prescribed with a Fitbit Alta HR tracker for a 24-week-self-directed activity and will receive motivational interviewing for 12 weeks (Immediate intervention group; during week 0 to week 12 and Delayed intervention group; during week 13 to week 24). The study protocol through 24 weeks is illustrated in Fig. 1.

**Fig. 1 Fig1:**
[figure not shown]
Study protocol through 24 weeks trial

#### Inclusion criteria

Female breast cancer survivors 18 years and older who are within 3 years of diagnosis and at least 6 months post active treatment; operation, chemotherapy and/or radiotherapy [stages 0 to 3 including those with ductal carcinoma in situ (DCIS)], will be recruited. Survivors on hormonal therapy such as, tamoxifen and aromatase inhibitors as well as immune targeted therapy (Herceptin) will be eligible to participate because these hormonal and cell surface blockages do not have direct effects on immune cells and adiposity-related biomarkers in breast cancer. The study will also include participants who are unable to read/ write English but are literate and English speaking. For participants with non-English literacy, translators will be used to obtain informed consent and the study will apply the questionnaires that have been validated in other languages such as Vietnamese, Greek, Chinese and Macedonian. This study plans to recruit participants from Breast cancer care service of Sunshine Hospital, Western Health, Melbourne, Australia.

